## Abstract

**Background:**

Transgender, nonbinary, and gender diverse (TGD) young adults face a disproportionately high mental health burden, including 2- to 4-fold increased risk of suicidality and depressive distress compared to their cisgender peers. Family and community support are protective factors that may mitigate these adverse outcomes, representing key targets for mental health interventions.

**Objective:**

This randomized controlled trial (RCT) evaluates the effectiveness of TransHealthGUIDE, a novel digital, app-based education and support intervention aimed at reducing past 3-month suicidal ideation and past 2-week depressive distress among TGD young adults. Participants are randomized 1:1 to an immediate intervention arm or a 6-month deferred intervention arm (waitlist control).

**Methods:**

From 2021 to 2024, a multidisciplinary team of academic and community partners conducted formative research and codeveloped a digital app containing 33 self-paced modules, communication, and interactive resources. The content is grounded in the Social Ecological Suicide Prevention Model and the Gender Minority Stress and Resilience Framework, designed to enhance family support and community connection for TGD young adults and their families. TGD young adults (ages 18-24 years) and their caregivers are prospectively enrolled and randomized in 10 US states (California, Connecticut, Illinois, Maryland, Massachusetts, New Jersey, New York, Oregon, Vermont, and Washington, DC). Participants complete self-reported surveys at baseline, 6 months, and 12 months, assessing sociodemographics, family support, community connection, suicidal ideation, depressive distress, and intervention acceptability. App usage and engagement are tracked via metadata. The target sample size is 500 TGD young adults, with 50% (n=250) identifying as people of color and 125 TGD young adult-caregiver dyads.

**Results:**

TGD young adult and caregiver communities, including our community advisory board (CAB), have guided all aspects of the project: study design (eg, waitlist control), survey development (eg, self-reported rather than clinician-administered suicidality measures and inclusion of social justice activism as a form of support), intervention content (eg, text, infographics, interviews with TGD people and caregivers, and simulations), and digital app safety features (eg, a quick-exit button for privacy). Recruitment and study screening began on January 21, 2025. As of May 2, 2025, a total of 149 individuals completed a study screener, with 132 (88.6%) of 149 found eligible. Enrollment visits began on April 23, 2025. As of May 2, 2025, five TGD young adults have been enrolled. Ongoing engagement with the CAB will inform iterative improvements throughout the trial.

**Conclusions:**

Scalable, app-based interventions tailored to meet the needs of TGD young people hold promise for population-level mental health impact. This RCT—targeting suicidality and depressive distress via education and support for both TGD young adults and their caregivers—addresses a critical gap in mental health interventions for this underserved population.

**Trial Registration:**

ClinicalTrials.gov NCT06177600; https://clinicaltrials.gov/study/NCT06177600

**International Registered Report Identifier (IRRID):**

DERR1-10.2196/78619

## Introduction

### Background

Transgender, nonbinary, and gender diverse (TGD) individuals experience multiple forms of interpersonal and structural stigma and face intersectional gender-, race-, and socioeconomic-based minority stress at various levels [1-4], including within their own families [5-8], resulting in life-threatening health disparities. Suicide, one of the top 10 causes of death in the United States and the second leading cause of death among young adults [9,10], is 2-4 times more likely to affect TGD young adults compared to their cisgender peers [11,12]. Rates of depressive distress are similarly elevated among TGD young adults [11-13], as are other mental health conditions such as nonsuicidal self-injury, anxiety, and substance use [11-14].

Compounding these disparities, TGD individuals are more likely than the general population to identify as Black or Hispanic, and they frequently experience race-based health inequities [15]. For Black and Hispanic communities, which already face a disproportionately high burden of suicide compared to the general population [16], these intersecting vulnerabilities further increase risk for Black and Hispanic TGD individuals.

There is an urgent need for evidence-based interventions that address the unique mental health challenges faced by TGD young adults. Research shows that family functioning and support—including communication, satisfaction, and acceptance—are protective factors for TGD individuals’ mental health [5,6,17,18]. Additionally, a strong sense of community connectedness is associated with improved mental health outcomes [19-21]. These findings emphasize the crucial role of supportive relational contexts—within families and communities—in promoting TGD individuals’ well-being. Self-guided digital mental health interventions, including web- and smartphone-based apps, have demonstrated effectiveness in reducing depression and suicidality among young people [22,23]. They have also been shown to increase perceived social support [24] and are generally well-accepted by individuals experiencing mental health concerns [25]. However, to our knowledge, no evidence-based digital app intervention currently exists that is designed to reduce depression and suicidality among TGD young adults, while also engaging their caregivers or families in the process.

### Study Objective and Aims

This prospective randomized controlled trial (RCT) evaluates the effectiveness of an educational and supportive app-based digital intervention in reducing suicidal ideation and depressive distress among TGD young adults across 10 US states. TransHealthGUIDE (Transforming Mental Health for Transgender and Gender-Diverse Young Adults Using Interventions to Drive Equity) is a co-designed digital app developed in partnership with TGD communities. The intervention engages, empowers, and fosters connections between TGD young adults and their families.

The primary aim of this study is to test the effectiveness of a digital app-based intervention in reducing past 3-month suicidal ideation and past 2-week depressive distress among TGD young adults and their caregivers, by comparing participants randomized 1:1 to an immediate intervention arm versus a 6-month deferred intervention arm (waitlist control).

The secondary aims are (1) to assess the impact of the intervention on family functioning (past 3-month family communication, satisfaction, and acceptance) and on community belonging and connection for TGD young adults and their caregivers, and (2) to examine the dyadic relationship dynamics between TGD young adults and their caregivers participating in the intervention.

## Methods

### Study Design

This is a prospective, digital RCT in which TGD young adults and their caregivers are randomized 1:1 to either an immediate intervention arm (a 6-month active intervention period followed by 6 months of observation) or a deferred intervention arm (a 6-month waitlist period followed by active intervention). Each participant is enrolled in the trial for a total of 12 months (see Figure 1). The total study duration is approximately 2 years.

**Figure 1 figure1:**
[figure not shown]
TransHealthGUIDE (Transforming Mental Health for Transgender and Gender-Diverse Young Adults Using Interventions to Drive Equity) study schema. Target sample size is 500 TGD young adults, with one-quarter (125 participants) in a dyad with a caregiver (target sample size of 125 caregivers). TGD: transgender, nonbinary, and gender diverse.

Participants in the immediate intervention arm receive full access to the TransHealthGUIDE digital app for the first 6 months. This is followed by a 6-month observation period during which they retain access to the app but receive no new intervention content or engagement prompts. Participants in the deferred intervention arm receive limited access to the app for the first 6 months, consisting primarily of curated local, regional, and national support resources. At the 6-month mark, participants in the deferred arm are granted full access to the digital app for the remainder of their participation.

Survey assessments are administered at baseline, 6 months, and 12 months to evaluate primary outcomes (past 3-month suicidal ideation and past 2-week depressive distress) as well as secondary measures.

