### Statistical Analysis

#### Power

The study aims to enroll 500 TGD participants between the ages of 18 and 24 years, 125 caregivers, and one-quarter of the young adult sample in a TGD young adult-caregiver dyad. The primary outcome of interest is past 3-month suicidal ideation.

Power calculations determined the sample size needed to detect a significant difference in suicidal ideation between the immediate and deferred intervention arms. To detect an effect size of at least 30% (risk ratio=0.70) in the reduction of suicidal ideation from baseline to 6 months postrandomization, a total sample size of 400 participants (200 per arm) is required to achieve 80% power at a 0.05 significance level.

We selected a 30% effect size threshold based on the assumption that smaller differences would not be clinically meaningful for public health scale-up. To account for an estimated 20% attrition rate, we plan to enroll 500 TGD young adult participants and 125 caregivers at baseline, yielding an anticipated analyzable sample of 400 TGD young adult participants and 100 caregivers.

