#### Primary Aim Analyses

The primary outcome is suicidal ideation in the past 3 months, assessed using the 6-item C-SSRS. The C-SSRS demonstrates strong validity, with 100% sensitivity and 99.4% specificity for identifying aborted suicide attempts, and 100% sensitivity and specificity for classifying interrupted and actual suicide attempts, when compared to clinician-administered instruments [41]. The secondary outcome is depressive distress over the past 2 weeks, measured using the Patient Health Questionnaire-9, where a score of ≥10 indicates a positive screen for symptoms of clinically elevated depressive symptoms (88% sensitivity and 88% specificity for detecting major depression) [43].

Before analysis, data will be audited for quality and completeness. Descriptive statistics—including counts, percentages, means, medians, standard deviations, and ranges—will summarize baseline characteristics. Group differences at baseline will be assessed using *t* tests for continuous variables and chi-square tests for categorical variables. Variables that differ significantly between study arms may be included as covariates in subsequent models. All analyses will be conducted using SAS or R statistical software.

To evaluate intervention effectiveness, we will use an intention-to-treat approach. Poisson generalized estimating equations with a log link function will estimate the population-average (marginal) effect of the intervention on suicidal ideation from baseline to 6 months postrandomization [60]. An unstructured correlation structure will be used to account for within-subject correlations across repeated measures (baseline, 3 months, and 6 months).

The primary endpoint analysis will compare the proportion of participants reporting suicidal ideation in the past 3 months between the immediate and deferred (waitlist control) arms. The model will include a common intercept and fixed effects for the intervention arm (immediate vs deferred) and time point (3 vs 6 months). Baseline characteristics that differ significantly between groups and variables related to missingness will be included as covariates, if appropriate.

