The primary estimate is the intervention arm assignment. The risk ratio will be estimated by exponentiating the intervention coefficient from the model. Wald tests with robust standard errors will be used to construct 95% CIs and test the primary hypothesis. For TGD young adult-caregiver dyads, we will adjust models to account for dyadic interdependence.

The same analytic approach will be applied to the secondary outcome of past 2-week depressive distress. Statistical significance will be determined at the 0.05 level.

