#### Secondary Aims Analysis

We will explore whether hypothesized mediators at month 3 and month 6 mediate the relationship between intervention arm assignment and suicidal ideation and depressive distress at month 12. We hypothesize that factors targeted by the intervention—namely, family communication, family satisfaction, family acceptance, and community belonging—will mediate the effects of the intervention on the primary outcomes: past 3-month suicidal ideation and past 2-week depressive distress.

Causal mediation analysis methods [62,63] will be used to estimate the total, direct, and indirect effects of each mediator individually, followed by their combined joint effect [64]. We will also calculate the proportion mediated to determine the extent to which each mediator (or the set of mediators) accounts for the total effect of the intervention. These mediation analyses will be conducted using a series of random effects logistic regression models.

Additionally, we will explore differences in family characteristics based on whether a supportive caregiver could be identified and agreed to participate. These comparisons will offer valuable insights for refining future intervention strategies. TGD young adult-caregiver dyads also complete an additional measure to assess the impact of joint participation on the dyadic relationship. We will further examine potential differences in outcomes between linked and unlinked dyads.

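### Depressive distress is labelled a primary outcome in two places and the secondary outcome in the analysis sections; the labels need to be reconciled

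*Protocol article*

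**What the plan says.** Two places in the protocol article give depressive distress primary status. In Methods, Study Design (the text after Figure 1), the surveys are given "to evaluate primary outcomes (past 3-month suicidal ideation and past 2-week depressive distress) as well as secondary measures". In Secondary Aims Analysis, the mediators are expected to carry the intervention's effect on "the primary outcomes: past 3-month suicidal ideation and past 2-week depressive distress".

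Two other sections give it secondary status. Power says: "The primary outcome of interest is past 3-month suicidal ideation", and bases the sample size on that outcome alone. Primary Aim Analyses says: "The primary outcome is suicidal ideation in the past 3 months, assessed using the 6-item C-SSRS", and then: "The secondary outcome is depressive distress over the past 2 weeks". The same section repeats the ranking when it sets the method: "The same analytic approach will be applied to the secondary outcome of past 2-week depressive distress". It closes with: "Statistical significance will be determined at the 0.05 level".

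Study Objective and Aims states the primary aim as testing effectiveness "in reducing past 3-month suicidal ideation and past 2-week depressive distress among TGD young adults and their caregivers". This names both outcomes but does not rank them as outcomes.

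**The concern.** The set of primary outcomes fixes what the trial must show to be called successful. Here the current text holds two such sets. Study Design even contrasts the two primary outcomes with secondary measures, so its label is hard to dismiss as loose wording. Secondary Aims Analysis belongs to the same Statistical Analysis part of the article as the two sections that say the opposite.

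The practical risk lies in a split result. If ideation misses and depressive distress reaches 0.05, one part of the article supports reporting success on a primary outcome, and another supports reporting a missed primary with a significant secondary. The article gives no rule on whether one or both outcomes would have to be significant. A statistical analysis plan that is not shown could settle the testing rule, but it could agree with only one of the two labels, so the article would still need correcting.

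**Working it through.** **1. The sections side by side**

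| Section | Suicidal ideation | Depressive distress |
|---|---|---|
| Study Design | primary | primary |
| Secondary Aims Analysis | primary | primary |
| Power | primary, and the only outcome powered | not mentioned |
| Primary Aim Analyses | primary | secondary (stated twice) |
| Study Objective and Aims | named in the primary aim | named in the primary aim, no outcome rank |

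The last row is compatible with either reading. Primary Aim Analyses itself places one primary and one secondary outcome under that aim. The conflict is therefore between the first two rows and the next two.

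**2. The plan's own figures**

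The significance level is 0.05. Power states 400 analysable participants for ideation at a risk ratio of 0.70, and 500 enrolled. The attrition step reproduces: 400 / (1 − 0.20) = 500. The 400 cannot be reproduced because no control-arm risk is stated. That does not affect this point, which needs only the significance level.

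**3. Error rate under each reading**

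Inputs: two outcomes, each tested at 0.05 (Primary Aim Analyses). Two-sided testing is assumed; the article does not state it, but the Wald tests with 95% intervals imply it. The correlation r between the two test statistics is not given, so a range is shown.

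*One primary outcome.* The chance of a false positive on the primary is 0.05.

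*Two primaries, both required.* The chance is at most 0.05. If both null hypotheses are true and the tests independent, it is 0.05 × 0.05 = 0.0025. It approaches 0.05 when one null is true and the other outcome is almost certain to be significant.

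*Two primaries, either one enough.* With both nulls true and (Z1, Z2) bivariate normal with correlation r:

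family-wise error = 1 − P(|Z1| < 1.96 and |Z2| < 1.96)

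For r = 0 this is 1 − 0.95² = 1 − 0.9025 = 0.0975. For other values the bivariate normal probability was computed numerically:

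| r | Family-wise error |
|---|---|
| 0 | 0.0975 |
| 0.3 | 0.0951 |
| 0.5 | 0.0907 |
| 0.7 | 0.0835 |
| 0.9 | 0.0704 |

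The largest value, at independence, is 0.0975 / 0.05 = 1.95 times the nominal level.

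**4. Error rate after the preferred fix**

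Under a fixed sequence, depressive distress is tested at 0.05 only if ideation is significant. If the ideation null is true, any false claim first requires a false rejection for ideation, with chance at most 0.05. If it is not true, the only possible false claim is on depressive distress, again at most 0.05. Family-wise error is at most 0.05 whatever the correlation.

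**The case against.** The strongest reply is that the sections governing the confirmatory test agree with each other. Power and Primary Aim Analyses name ideation as the primary outcome, the sample size is for ideation, the primary endpoint analysis compares ideation, and there is one primary hypothesis. The competing label sits in a sentence about the survey schedule and in an exploratory mediation section. The ranking in the analysis sections was also public with only five participants enrolled, and the article states that analysts and investigators are blinded. Most of this stands. It makes ideation the natural reading and the repair simple, but it does not remove the two contrary statements.

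A reader might infer more than the article supports:

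- *That a positive trial is undefined.* Power and Primary Aim Analyses do define one. The fault is that two other sections use a different set of primary outcomes.
- *That the error rate nearly doubles.* This needs two primary outcomes, a rule that either suffices, and independent tests. The rule is not stated, and independence is implausible for two mental health outcomes in the same people.
- *That the primary aim is a third contradiction.* It is an aim covering both outcomes, and one primary plus one secondary outcome fits under it.
- *That the missing testing order, or sizing the trial on ideation alone, is a fault in itself.* With ideation as sole primary, an order for a secondary outcome is commonly left to the analysis plan, and powering on the primary alone is normal practice.
- *That the trial loses a known amount of power.* Any such figure needs a control-arm risk, which the article does not give, and describes an alpha split that nobody has proposed.

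**Conclusion.** The contradiction is real and lies in the current text: Study Design and Secondary Aims Analysis against Power and Primary Aim Analyses. Its effect on the error rate is conditional. Read as the analysis sections are written, the trial keeps its primary error at 5%, and it would also stay at or below 5% if both outcomes had to be significant. If the two-primary label were followed and either outcome sufficed, family-wise error would be about 8.3% to 9.1% at correlations of 0.7 to 0.5, and no more than 9.75%. These figures assume two-sided 0.05 tests, jointly normal test statistics and no effect on either outcome; the correlations are assumed, not taken from the article. The point deserves correction because the status of depressive distress should be settled before outcome data accrue, and at the reporting date enrollment had barely begun.

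**What to change.** State throughout that past 3-month suicidal ideation is the sole primary outcome, as Power and Primary Aim Analyses already do, and that past 2-week depressive distress is the key secondary outcome.

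- Correct the wording in Study Design and in Secondary Aims Analysis.
- In Study Objective and Aims, add that the primary aim covers one primary and one key secondary outcome.
- Preferably, state that depressive distress is tested at 0.05 only if ideation is significant.

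Settle the time point of the primary estimate separately. The model in Primary Aim Analyses has a single arm coefficient and a time effect for months 3 and 6, so restricting the primary outcome to one visit is a different decision from the ranking of outcomes.

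The relabelling changes wording only; sample size, procedures and participant burden are unaffected. The fixed sequence adds one testing rule. Its cost is that depressive distress cannot support a confirmatory claim if ideation misses; its result would then be reported as an estimate with its interval. If the sponsor prefers to keep both outcomes primary, the article must instead say whether one or both must be significant, how the 0.05 is allocated or ordered, and what power depressive distress has.

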### Project History and Multidisciplinary Team

In 2021, the National Institutes of Health (NIH) Common Fund launched the “Transformative Research to Address Health Disparities and Advance Health Equity” initiative. The goal of this initiative was to support innovative, translational research projects aimed at preventing, reducing, or eliminating health disparities and advancing health equity [26]. This grant mechanism specifically supported groundbreaking interventions targeting one or more NIH-designated populations that experience health disparities in the United States. Notably, pilot data were not required; instead, emphasis was placed on the development and implementation of novel, creative interventions.

Our multidisciplinary team chose to focus on the persistent mental health disparities affecting TGD young adults, particularly elevated rates of suicidal ideation and depressive distress. To address this urgent need, we conducted extensive formative research to develop a digital, app-based intervention designed to reduce these disparities by increasing family support and community connection.

The intervention was developed through a community-engaged process and reflects the combined expertise of a multidisciplinary team with backgrounds in TGD health, educational and curriculum design, sociobehavioral interventions, digital health development, clinical trials, psychiatry and mental health, young adult developmental psychology, family systems, and TGD lived experience. TGD young adults and caregivers were actively involved throughout the development process, ensuring that the intervention was relevant, affirming, and grounded in real-world experiences.

